### Outcomes

#### Primary outcomes

EEG data will be the primary outcome measure and recorded before and after the treatment. During EEG recording, subjects will be in a quiet room and wear a 64-lead Waveguard Original (CA-208, ANT neuroo, the Netherlands) Ag/AgCl EEG cap, keeping their eyes closed. EEG data will be collected with an electrode distribution according to the international 10–20 standard. EEG recordings will be performed with the company’s eego64 acquisition software, version 1.8.2, with the CPz and AFz electrodes used as the reference and ground electrodes, respectively. The sampling frequency will be 1000 Hz, and the electrode impedance will be reduced to less than 5 kΩ for each recording.

The preprocessed data will be transformed into a binary matrix to measure brain network parameters, including global efficiency, local efficiency, node degree, and node betweenness centrality.

Each index will be calculated as follows:

Global efficiency

$${E}_{\text{g}\text{l}\text{o}\text{b}}=\frac{1}{N\left(N-1\right)}{\sum }_{i\ne \dot{J}{\epsilon}V}\frac{1}{{l}_{ij}}$$

where $$V$$ is the set of all nodes, and $${l}_{ij}$$is the shortest path length of node $$i$$ and node $$j$$ (i.e., the path with the least number of edges).

b.Local efficiency

$$E\left(i\right)=\frac{1}{{N}_{Gi}\left({N}_{Gi}-1\right)}{\sum }_{\dot{J}\ne k{\epsilon}{G}_{i}}\frac{1}{{l}_{jk}}$$

$${E}_{loc}=\frac{1}{N}{\sum }_{i{\epsilon}V}E\left(\dot{i}\right)$$

where $$E\left(i\right)$$ represents the local efficiency of node $$\dot{i}$$, $${G}_{i}$$ is the subgraph formed by the neighbors of node $$\dot{i}$$, and $${l}_{jk}$$ denotes the shortest path length of node j and node $$k$$.

c.Degree.

Degree refers to the number of edges connected to a node. To analyze the constructed brain network and the neuromodulation effect of acupuncture, the node degree was selected for objective evaluation and analysis.

d.Betweenness centrality

$${N}_{bc}\left(i\right)={\sum }_{\dot{J}\ne i\ne k{\epsilon}G}\frac{{\sigma }_{jk\left(i\right)}}{{\sigma }_{jk}}$$

where $${\sigma }_{jk}$$ denotes the number of shortest paths from node $$\dot{J}$$ to node $$k$$, and $${\sigma }_{jk\left(i\right)}$$denotes the number of shortest paths that pass through node $$\dot{i}$$.

#### Secondary outcomes

Regarding secondary outcomes, the Wisconsin Card Sorting Test (WCST) will be used to assess cognitive function. The WCST is an evaluation tool used to measure cognitive abilities, such as abstract thinking, attention shifting, information memorization, and recognizing and responding to stimuli. It is highly sensitive to damage to the dorsolateral prefrontal cortex [18]. The PSQI will be used to assess sleep quality. It is an internationally recognized tool for assessing sleep quality that is suitable for use in patients with sleep disorders and in the general population [19, 20]. The timeline of each assessment is shown in Table 1.

**Table 1 Tab1:** Participant timeline

Study Flow Chart						
Phase	Baseline period	Period of treatment		Period of follow-up		
Number of visits	1	2	3	4	5	6
Time (weeks)	Week 0	Week 4	Week 8	Week 12	Week 16	Week 20
Inclusion/exclusion criteria	**√**					
Informed consent obtained	**√**					
Demographic data	**√**					
Medical history and treatment history collected	**√**					
Pittsburgh Sleep Quality Index (PSQI)	**√**	**√**	**√**			**√**
Wisconsin Card Sorting Test (WCST)	**√**	**√**	**√**			**√**
EEG acquisition record sheet	**√**		**√**			**√**
Adverse event acupuncture record	**√**					
Combined medication records	**√**					
Adverse event (AE) recording form	**√**					
Serious Adverse Event (SAE) report form	**√**					
Treatment-Emergent Symptom Scale	**√**					
Assessment of adherence	**√**					
Study completion	**√**					
Review by investigators	**√**					

### Other measures

Researchers will identify any adverse effects through patient self-reports and monthly inquiries. All adverse events will be addressed, documented, and classified according to their relevance to acupuncture therapy. Researchers must inform the principal investigator and the Data and Safety Monitoring Board (DSMB) of serious adverse events within 24 h. Additionally, the subjects’ compliance and treatment side effects will also be recorded in the study.

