### Randomization and blinding

The “Proc plan” feature of SAS 9.3(SAS Institute Inc., Cary, NC, USA) will be employed to create the necessary random allocation plan for the study. Eligible subjects will be assigned to Group A (electroacupuncture plus placebo drug), Group B (drug plus placebo electroacupuncture), or Group C (placebo electroacupuncture plus placebo drug) at a ratio of 1:1:1. All patients will be seen by appointment. During the acupuncture intervention, which will be completed in a quiet, separate treatment room to avoid contact and communication between patients in different groups, the therapist will instruct the patient to close their eyes. Only the acupuncturist performing the needle insertion throughout the trial will be aware of the patient’s group allocation. The subjects, evaluators of therapeutic effects, and individuals conducting the statistical analysts will be blinded to group allocation.

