### Intervention

The treatment in this project will be administered by a professional acupuncturist with more than 3 years of experience. Treatment will be administered three times a week, with a minimum of 24 h between each session, over 8 weeks (24 treatment sessions).

An SDZ-V type Hua Tuo brand electronic acupuncture treatment instrument and needles (0.30 × 25 mm) will be used in this trial. Both the needles and the electroacupuncture device will be purchased from Suzhou Medical Supplies Factory Co., Ltd. (Production Enterprise License: Su Shi Yao Jian Xie Chan Xu 2001-0020; Registration Certificate Number: Su Shi Yao Jian Xie (Zhun) Zi 2004 No. 2,270,202).

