### Drug

For a continuous treatment period of 8 weeks, 10 mg of zopiclone hydrochloride tablets will be taken orally before bedtime every day. The drug registration number is H20090001, the import permit number for psychotropic drugs is TPI20090302 and the approval number for imported drug packaging is National Drug Approval J20090050.

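### The only active questioning about adverse effects that the protocol states is monthly, although patients attend three times a week, so brief events depend on spontaneous report or about four weeks of recall

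*Protocol article*

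**What the plan says.** Under Other measures, the protocol article names two routes for finding harms: "Researchers will identify any adverse effects through patient self-reports and monthly inquiries". The same section has events documented and classified by their relation to acupuncture, and has side effects and compliance recorded.

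The contact schedule is much denser. Intervention states: "Treatment will be administered three times a week, with a minimum of 24 h between each session, over 8 weeks (24 treatment sessions". Drug states that the tablets "will be taken orally before bedtime every day" for 8 weeks, and Placebo drug matches that schedule. All three arms receive needling (real or sham) and tablets (active or placebo), so the schedule is the same in every arm.

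On blinding, Randomization and blinding states: "Only the acupuncturist performing the needle insertion throughout the trial will be aware of the patient’s group allocation". It continues: "The subjects, evaluators of therapeutic effects, and individuals conducting the statistical analysts will be blinded to group allocation". No one is named there as assessor of harms.

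For timing, Secondary outcomes states: "The timeline of each assessment is shown in Table 1". That table has columns at weeks 0, 4, 8, 12, 16 and 20. Its rows include an "Adverse event acupuncture record", a "Treatment-Emergent Symptom Scale", a general adverse event form and a serious adverse event form.

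**The concern.** The stated frequency of active questioning does not match how often patients are exposed and seen. Local pain or bleeding after needling, dizziness, and drowsiness the next morning can come and go within hours or a day. A question asked once a month will find such events only if the patient still remembers them and thinks them worth mentioning. Between inquiries the stated route is self-report, and how readily patients volunteer minor events varies.

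What is at stake is the harms comparison between electroacupuncture, drug and double placebo. Under-capture of minor events makes the harms profile incomplete in all three arms. It may also narrow real differences, because brief events are those for which real and sham needling, or drug and placebo, could differ most visibly. The Abstract promises strict monitoring of adverse events, and a monthly question fits that poorly when patients are on site three times a week.

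**Working it through.** **Inputs**
- Sessions: 3 per week for 8 weeks (Intervention).
- Tablets: one dose each night for 8 weeks (Drug; Placebo drug).
- Active inquiry: monthly (Other measures).
- Visits after baseline within treatment: weeks 4 and 8 (Table 1).
- Patients: 120 (Sample size).

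**Step 1. The plan's own figure.** 3 × 8 = 24 sessions. This reproduces the stated 24.

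**Step 2. Doses.** 8 × 7 = 56 nights.

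**Step 3. Active inquiries during treatment.** The text says only that inquiries are monthly. If they coincide with the four-weekly visits, they fall at weeks 4 and 8, which gives 2. If instead a month is 30 days, the second inquiry falls on day 60, after treatment ends on day 56, which leaves 1. The range is therefore 1 to 2, and 2 is used below because it is the more favourable to the plan and matches Table 1.

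**Step 4. Exposure per inquiry.** 24 / 2 = 12 sessions and 56 / 2 = 28 nightly doses per active inquiry. With full attendance of 120 patients, there are 120 × 2 = 240 inquiries during treatment and 120 × 24 = 2,880 attended sessions. These figures describe opportunity to ask. They are not a count of missed events.

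**Step 5. Could Table 1 supply more frequent questioning?** In the text version, the only tick for the acupuncture record and the symptom scale is at week 0. The rows for study completion and investigator review also show a tick only at week 0, and those cannot be baseline-only. Merged cells have probably been lost, so no conclusion rests on those ticks. The columns are four-weekly, with none for individual sessions. If the forms are completed at every visit, structured questioning is still four-weekly. If a merged cell means continuous recording, that fixes when an event is written down but not how often the patient is asked.

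**Step 6. Who hears the self-reports?** Other measures assigns identification of events to researchers in general. Randomization and blinding says who knows the allocation but not who takes reports of harm. The acupuncturist is the one person certain to be present at each session, and is not blinded. The text goes no further than that.

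**The case against.** **The harms instruments already exist.** Table 1 lists an acupuncture-specific record and a symptom scale, both directly relevant to the events at issue. This stands in part. The text does not establish that nothing structured happens more often than monthly; it establishes that monthly is the only interval stated for active questioning. It also means that the remedy should reuse these forms rather than add new ones.

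**An article condenses the full protocol.** Who completes a form, at which contact and in what words normally sits in the full protocol or case record form. This also stands: silence on the recipient of self-reports is not in itself an error. The interval, however, is something the article does state.

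**No planned result changes.** Harms are neither primary nor secondary outcomes, and Statistical analysis specifies no harms comparison. This is correct, and it is why the point is minor.

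**The unblinded acupuncturist.** A reader might infer that self-reports are made at sessions to the acupuncturist, so that recording depends on knowledge of the arm. The inference is plausible, but no section says so, and the researchers who identify events may include blinded staff. It is not part of this point.

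**Conclusion.** The point holds as a modest weakness in a stated method. Active inquiry about adverse effects is fixed at monthly, which gives about 2 inquiries against 24 sessions and 56 nightly doses per patient. That count assumes inquiries at weeks 4 and 8 and no unstated questioning at sessions. Brief needling or next-day tablet effects therefore depend on spontaneous report or about four weeks of recall.

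How many events would be missed cannot be derived from the document. A reader might put the chance of recalling a minor event at the monthly question at 30–60% and conclude that 40–70% of unvolunteered minor events are lost (1 − 0.6 = 0.4; 1 − 0.3 = 0.7). That loss is only the complement of an assumed figure, and it applies to an unknown number of events, so it should not be cited as a size.

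The article does not settle whether the person who receives self-reports is blinded. No sample size, alpha, power or efficacy analysis is affected. Acting on the point would be a low-cost improvement to safety data; it is not a condition for the trial's validity.

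**What to change.** Amend Other measures as follows.

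- At each of the 24 sessions, the patient completes a short yes/no self-report with fixed wording, covering events since the last session and the last tablet. It should use or adapt the existing acupuncture adverse event record.
- The wording and timing are identical in all three arms.
- Positive items are transferred to the existing adverse event form.
- The monthly inquiries are kept for the follow-up period.
- The section states who receives the self-reports and whether that person is blinded.

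**Cost.** At about one minute per session, this is 24 minutes per patient, or 2,880 / 60 = 48 hours over 120 fully attending patients. More minor events will be recorded in all arms, which the report should explain.

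**Risk to manage.** Sham needles do not penetrate the skin (Sham electroacupuncture), so answers to needling-specific items may hint at the arm. Whoever handles the forms should therefore not be an efficacy evaluator. Routine blinded review of every checklist is not recommended: it adds staff work and could itself reveal the arm to the reviewer.

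**Timing.** Trial status says that recruitment began on 1 September 2022. If the change is made partway, record its date so that harms collected before and after can be told apart.

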### Placebo drug

A placebo drug composed of starch will be administered with the same appearance, administration method, and treatment duration as the positive control drug.

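### In Study 2 the only causality rule stated for adverse events names acupuncture and not the study tablets, so a related-events table built on it could omit drug harms

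*Protocol article*

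**What the plan says.** The causality rule stands in the protocol article under Other measures: "All adverse events will be addressed, documented, and classified according to their relevance to acupuncture therapy". The same paragraph has compliance and side effects of treatment recorded, and serious events reported to the principal investigator and the DSMB within 24 h.

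Randomization and blinding sets the Study 2 arms as "Group A (electroacupuncture plus placebo drug), Group B (drug plus placebo electroacupuncture), or Group C (placebo electroacupuncture plus placebo drug) at a ratio of 1:1:1". Every arm therefore combines a needling component with a tablet component.

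The Drug section gives the active exposure in Group B: "For a continuous treatment period of 8 weeks", the "tablets will be taken orally before bedtime every day". It cites a psychotropic permit ("the import permit number for psychotropic drugs is TPI20090302"). The Placebo drug section matches the dummy to it: "A placebo drug composed of starch will be administered with the same appearance, administration method, and treatment duration as the positive control drug".

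Table 1 lists a general adverse event form, a serious adverse event form, a Treatment-Emergent Symptom Scale and a separate acupuncture adverse event record. It lists no corresponding record for the tablets. Sample size plans 40 patients per group and 120 in total.

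**The concern.** A double-dummy trial has two possible sources of treatment-related harm in every arm. The rule asks about one of them. In Group A it asks about the active treatment. In Group B it asks about the sham, while the active treatment in that arm is the tablet. An event caused by the drug can only be filed as unrelated to acupuncture, in the same class as an intercurrent illness.

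What is at stake is how harms are attributed. The Discussion paragraph of the abstract presents electroacupuncture as a possible alternative treatment, so readers will want its harms set against those of the drug. If the report tabulates related events by the only class the article defines, the two active arms are not measured by the same standard. A serious event would also be classed under this rule with an acupuncture judgement and no drug judgement.

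**Working it through.** **Step 1: how many patients are concerned.** The figure of 40 comes from Sample size. Inputs there are means 9.8 and 13.9, SDs 3.1 and 3.2, the value 1.5, α = 0.025, power 0.90 and dropout 20%. Reading 1.5 as the superiority margin and α as one-sided:

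- difference = 13.9 − 9.8 = 4.1; net of margin = 4.1 − 1.5 = 2.6
- unequal-variance t test, noncentral t: n = 32 per group, power 0.901 (the normal approximation gives 31)
- after dropout: 32 / (1 − 0.20) = 40 per group; 3 × 40 = 120

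The article's figure is reproduced. By plan, 40 Study 2 patients take active tablets and 120 − 40 = 80 take placebo tablets. Study 1 describes no tablets, so the point concerns Study 2 only.

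**Step 2: apply the rule to each arm.**

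| Group | Needling | Tablets | What the rule asks about | What it does not ask about |
|---|---|---|---|---|
| A | real | placebo | the active treatment | placebo tablets |
| B | sham, no skin penetration | active | the sham | the active treatment |
| C | sham, no skin penetration | placebo | the sham | placebo tablets |

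The rule is worded identically for all arms, but it reaches the active treatment in A and misses it in B.

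**Step 3: which comparisons are affected.** In arm g, let x_g be the number of patients with an event caused by needling or stimulation, t_g the number with an event caused by tablets, and u_g the number with an event from another cause. For simplicity, assume no patient has more than one kind and that attribution is correct.

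- Any event by arm: (x_g + t_g + u_g) / 40. No causality class enters, so A, B and C are treated alike.
- Related events under the stated rule: x_g / 40. For A this contains the harms of the active treatment. For B it contains only x_B, and t_B is left out.
- Related events with both classes recorded: x_g / 40 and t_g / 40 for each arm. Both active treatments are covered.

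**Step 4: size.** The number left out of a related-events table for Group B is t_B. The article gives no event rate for the drug, so t_B can lie anywhere from 0 to the 40 planned patients. Misattribution to needling could bring a few of these events back into the table, so even full omission is not certain. Adding the second class changes no sample size or other figure in the plan.

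**The case against.** The strongest reply is that the article does not call this the sole classification. The same paragraph records side effects of treatment without limiting them to acupuncture. Table 1 keeps the acupuncture record apart from the general forms, which suggests that safety capture is wider than acupuncture. Causality fields usually sit on forms that a journal article does not print. Statistical analysis plans no table of related events, safety is neither a primary nor a secondary outcome, and incidence by randomised arm needs no causality class.

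Most of this stands, and it rules out three stronger readings that a reader might infer:

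- *Drug harms go unrecorded, or the whole safety comparison is biased.* Not supported. All events are documented in all arms, and all-event incidence stays symmetric.
- *The DSMB receives no drug-causality information.* Not supported. The article gives the reporting time for serious events but does not describe the content of the report.
- *The size can be read from counts of tablets against needling sessions.* Not supported. These are planned exposures in unlike units, and causality classes attach to events.

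The reply does not remove the core. The article does not leave causality to another document: it states a rule, applies it to all adverse events, and names one of the two interventions. The general forms and the symptom scale show that events are captured. Nothing in the article gives any of them a drug-relatedness judgement.

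**Conclusion.** The point holds in limited form. The only causality rule stated for Study 2 omits the tablets that all three arms take, including the active drug planned for 40 Group B patients. Any tabulation of treatment-related events built on that rule could show electroacupuncture harms in Group A and omit drug harms in Group B. The rule also calls for no drug-relatedness judgement on serious events. All-event incidence by arm, the efficacy analyses and the sample size are untouched.

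This assumes that the rule is applied as worded and that the unseen forms do not already hold a drug-relation field. If they do, the practice is sound and only the sentence needs correcting. The number of misplaced events cannot be estimated from the article. The change is worth making because it is cheap and the gap lies in a rule the article itself sets.

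**What to change.** Reword the sentence in Other measures so that each adverse event in all three groups is classified for relation to (a) needling or electrical stimulation and (b) study tablets, active or placebo. The judgement should be made blind to allocation. By Randomization and blinding, only the acupuncturist knows the group, so the assessor should be someone else. Apply both classes to serious events as well.

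State that the arms will be compared on all treatment-emergent events regardless of relatedness, with relatedness as a secondary tabulation.

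The cost is at most one extra field on the adverse event form. Trial status has recruitment running from 1 September 2022 to the end of December 2024 and provides for notifying modifications. Because all events are documented, those already recorded can be given the second class retrospectively, as far as the records allow.

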### Data management

Case record forms will be used to collect and manage scale data, while EEG data will be securely stored on specialized hard drives monitored by the Data and Safety Supervision Committee. We will share the trial data before May 2025. The researchers can be contacted to obtain the data.

### Data availability statement

The minimum retention period for the data is 5 years after publication. The Principal Investigator will have access to the final test dataset, and the corresponding author can be contacted to access the test data. The patient’s identity, age, and phone number will remain confidential.

### Quality control

Experts in acupuncture and moxibustion, psychiatry, statistics and methodology reviewed and provided feedback on the test protocol. Before beginning the experiment, all researchers will be instructed on how to screen patients, administer the scales, perform acupuncture, and enter the data.

